### **Exploratory outcomes**

Exploratory outcomes include the following:

- Change in SARS-CoV-2 RNA level (Polymerase chain reaction, Cycle Threshold value) in oral or nose/throat swab samples at days 3, 14, 28 and 180 after randomisation (cohort 2 only)
- Change in anti-SARS-CoV-2 spike antibody levels in blood at days 14 and 28 after randomisation
- SARS-CoV-2 whole-genome sequence analysis in oral or nose/throat swab samples at day 1 and 28 after randomisation
- Proportion and clinical characteristics of patients with cultivable virus at day 28, hospitalisation and day 180
- Virus sequence variation and cultivability over time, overall and in individuals receiving vs not receiving CP

Summaries for biomarkers (i.e., exploratory endpoints) will be provided by treatment group and collection time. Additional exploratory analyses may be performed and will be specified in the SAP, as appropriate.

### **Subgroup analyses**

Exploratory analyses of safety and efficacy will be conducted in subgroups of subjects including but not limited to SARS-CoV-2 variant identified at inclusion, SARS-CoV-2 vaccinal status at inclusion, anti-SARS-CoV-2 MoAbs received, and the cumulative dose of antibody received. The interactions between experimental treatment and vaccinal status as well as the dose of antibody received will be explored and tested.

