## I. STUDY PRESENTATION - CONTEXT

The COVIC-19 study is a prospective randomized clinical study evaluating the benefit of COVID-19 convalescent plasma (CCP) with a very high antibody titre administered early, on an outpatient basis, to vulnerable patients to prevent the progression of a COVID-19 disease to a severe form requiring hospitalization. The vulnerable patients concerned by this study are patients with recently diagnosed COVID-19 disease who do not need hospitalisation and who are: at least 70 years old; younger patients with risk factors for severe COVID-19; and patients with primary or secondary immunodeficiency. Patients randomized to the treatment arm will receive 2 units of CCP with high titre anti-SARS-CoV-2 antibody on an outpatient basis within 7 days of the onset of symptoms of COVID-19. Patients in the control group will not receive a specific intervention.

This study is based on growing evidence for the effectiveness of passive immunotherapy, by transfusion of CCP or administration of monoclonal antibodies, as long as treatment is carried out early after the diagnosis of the disease. In a recent randomized clinical trial in Argentina by Libster et al, the administration of CCP less than 3 days after the onset of symptoms of COVID-19 in vulnerable patients halved the risk of developing severe COVID-19 disease compared to a control group (16% after CCP transfusion vs. 31% without transfusion). Similar findings were recently reported in a clinical trial coordinated by the John Hopkins Hospital (USA). A third randomized trial found similar results as well for patients included less than 5 days after symptoms initiation. A 4th study did not confirm this efficacy of CCP, with however inclusion criteria that differed significantly (patients recruited in emergency rooms).

Importantly, a significant antibody dose response was observed. Likewise, the early administration of monoclonal anti-SARS-CoV-2 antibodies in mono- or bitherapy has been associated with a decrease in the frequency of hospitalization for COVID-19 disease.

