## **IV. STUDY DESIGN**

### **IV-1. Overall design**

COVIC-19 is a multicentre international, randomised, open-label adaptive superiority phase III trial to evaluate the efficacy and safety of COVID-19 convalescent plasma in the treatment of COVID-19. It is conducted in a harmonized approach in different countries in Europe.

The study is randomizing adult COVID-19 patients to one of two arms (1:1 ratio): standard of care or standard of care and very high neutralizing Ab titre convalescent plasma. Randomization will be stratified by centre and by patient cohort. The control group will receive 'standard care' therapy. Neither blinding nor placebo will be used to avoid unnecessary intravenous access.

Standard of care therapy may include anti-SARS-CoV-2 specific medication listed as authorized in a dedicated appendix. Centres should ensure that medications used as standard of care are used similarly for patients in both treatment arms.

Participating patients will be included in 2 cohorts of vulnerable patients (cohort 1: unvaccinated elderly ( $\geq 70$  years) and younger with comorbidities (cohort 1:  $< 70$  with comorbidities), cohort 2: immunosuppressed patients).

All subjects will undergo a series of efficacy and safety assessments, including laboratory assays. Subjects will be assessed at baseline, and at Days 3, 14, 28, 90 and 180.

Nasopharyngeal swabs (NP) or lower respiratory tract samples will be obtained at D1 (pre-treatment), and at D3, D14, D28 and D180 (and monthly in case of positivity until of clearance) for cohort 2 and on the day of hospitalization (if applicable).

Blood samples will be obtained at D1, D14 and D28 and on the day of hospitalization (if applicable).

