## **V-2. Exclusion criteria**

### **V-2-1. Unvaccinated elderly and high COVID-age population:**

1. Age < 18 years
2. Prior or concurrent treatment for COVID-19 (unless listed as authorized specific treatment)
3. History of documented SARS-CoV-2 infection in the last 90 days prior to enrolment
4. Prior anti-SARS-CoV-2 immunization
5. Contraindication to receiving CCP including previous history of transfusion-related acute lung injury (TRALI) or moderate or severe allergic reaction to blood components
6. Known participant objection to receiving plasma products
7. Primary or acquired immune deficiency listed below (see cohort 2)
8. Refusal to participate expressed by patient or legally authorised representative
9. Pregnancy

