### **X-3. Statistical analysis**

#### **General principles**

All analyses for reports, presentations and publications will be prepared by the coordinating centre at the Research Methods Unit (uMETH) of the Clinical Investigation Centre, University Hospital of Besançon. A more detailed statistical analysis plan will be developed by the investigators whilst still blind to any analyses of aggregated data on study outcomes by treatment allocation.

Although conducted as a single trial with randomisation stratified on the groups of patients (cohort 1 and 2) for operational and logistical reasons, the findings in each cohort are considered as separate trials and are analysed separately.

The final results will be reported according to the recommendations of CONSORT 2010.

All outcomes will be analysed in superiority (two-sided) analyses using simple hypothesis tests. As sensitivity analyses, generalized linear models will be used to account for stratification on the centre. No correction for multiplicity and no hierarchical testing procedures are planned in analysing secondary outcomes. These analyses will therefore be considered as exploratory in nature.

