#### **Subgroup analyses**

At the end of the study, subgroup analyses for the primary endpoint will be performed according to SARS-CoV-2 vaccinal status at inclusion and the cumulative dose of antibody received. The interactions

between experimental treatment and vaccinal status as well as the dose of antibody received will be explored and tested

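### The planned treatment-by-antibody-dose interaction cannot be estimated in either cohort, and the treatment-by-vaccination interaction cannot be estimated in cohort 1

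*Protocol*

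**What the plan says.** Protocol section X-3 has two paragraphs headed Subgroup analyses. The first follows the primary endpoint analysis and plans subgroups for that endpoint "according to SARS-CoV-2 vaccinal status at inclusion and the cumulative dose of antibody received". The second follows the exploratory outcomes. It covers safety and efficacy, calls its analyses exploratory, and gives an open list that ends "anti-SARS-CoV-2 MoAbs received, and the cumulative dose of antibody received". Both commit to the same tests: "The interactions between experimental treatment and vaccinal status as well as the dose of antibody received will be explored and tested".

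Other sections fix what values these two variables can take:

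- **Control arm.** Section I: "Patients in the control group will not receive a specific intervention". Section IV-1: "Neither blinding nor placebo will be used to avoid unnecessary intravenous access". Section VII-4 gives plasma to the CCP arm only.
- **Cohort 1.** Section V-1 defines it as unvaccinated, and section V-2-1 lists "Prior anti-SARS-CoV-2 immunization" as an exclusion. Section VI-4-1 records vaccination details for cohort 2 patients only.
- **Separate analysis.** Section X-3, General principles: "the findings in each cohort are considered as separate trials and are analysed separately".
- **Analysis set.** Section X-1-2 puts every efficacy analysis on the intention-to-treat population, by allocated arm and regardless of what was actually received.

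**The concern.** A treatment-by-modifier interaction asks whether the difference between arms changes across levels of a variable that patients in both arms have. CCP antibody dose exists in one arm only and is known only after randomisation. Vaccinal status is a proper baseline variable, but in cohort 1 everyone has the same value.

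Antibody dose is central to the trial's rationale (sections I, II-3-3, II-6 and VII-6), so readers will look for this result. As written, the analyst must either report that a planned test could not be done or replace it with a comparison of plasma recipients by dose. If that comparison were presented as an interaction test, it would look as if randomisation supported it, and section X-4 would let it be called significant at 0.05.

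**Working it through.** The plan gives no figure for these interactions, so this is a check of what the data can identify. The design size is used only to set the number of rows.

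**1. Design size.** Section X-2 states 0.15 versus 0.30, two-sided alpha 0.05, 90% power and 158 per group. The unpooled Z formula reproduces it: (1.960 + 1.282)² × (0.30×0.70 + 0.15×0.85) / 0.15² = 10.51 × 0.3375 / 0.0225 = 157.6, rounded up to 158. The plan raises this to 170 per group, so a cohort has 340 patients.

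**2. Treatment by dose.** Let T = 1 for CCP and 0 for control, and let D be the CCP antibody dose received. The interaction model has linear predictor b0 + b1·T + b2·D + b3·T·D.

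- Controls: T = 0 and D = 0, so the predictor is b0.
- CCP arm: T = 1, so the predictor is b0 + b1 + (b2 + b3)·D.

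Only the sum b2 + b3 can be learned. T·D equals D in every row, because both are zero in controls and both equal D in the CCP arm. With 170 per arm and illustrative dose values, the four-column matrix has rank 3. More patients or a different link function would not change this. Without the product term, the model with T and D has full rank (3 of 3). Its dose coefficient is then simply the dose slope within the CCP arm.

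**3. Dose as a subgroup.** A control patient cannot be classed as low or high dose, so no dose subgroup contains both arms. What remains is each CCP dose stratum against all controls. Randomisation does not protect that contrast, and it defines groups by treatment received, which section X-1-2 rules out for efficacy. Section II-3-3 shows how much conditioning on events around infusion can matter. In the randomised trial used for the sample size, excluding 6 of 160 patients (3.75%) who had an endpoint event before infusion moved the relative risk from 0.52 to 0.40. This illustrates sensitivity; it does not estimate the bias here.

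**4. Treatment by vaccinal status.** Let V = 1 if vaccinated.

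- Cohort 1: V = 0 for every eligible patient. The columns V and T·V are both zero, and the matrix has rank 2 of 4.
- Cohort 2: nothing requires patients to be unvaccinated, and one inclusion route requires a completed vaccination schedule. With an illustrative mix of vaccinated and unvaccinated patients, the matrix has rank 4 of 4 and the interaction is estimable.

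**5. Result by cohort.**

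| Planned interaction | Cohort 1 | Cohort 2 |
|---|---|---|
| Treatment × antibody dose | not estimable | not estimable |
| Treatment × vaccinal status | not estimable | estimable |

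**The case against.** **These analyses are secondary.** This stands. The second subgroup paragraph calls them exploratory, and the primary Z-test, sample size and interim rule do not use them. Software would drop or flag the aliased term, so no other estimate is biased.

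**The statistical analysis plan may settle the detail.** It could define dose strata and models, but it cannot make this interaction estimable. It could only substitute another analysis for the one the protocol states.

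**The sentence could be read differently.** It might mean the treatment-by-vaccination interaction and, separately, dose itself. The grammar allows this, and a dose-response can be fitted. But the reading is strained, because the primary-endpoint paragraph also names dose as a subgroup variable for a treatment comparison: "SARS-CoV-2 vaccinal status at inclusion and the cumulative dose of antibody received".

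**Antibody could include monoclonals.** The appendix authorises these in both arms, so some controls would then have a non-zero dose and the matrix would reach full rank. But the second paragraph lists monoclonals as a separate item, and section VII-6 uses antibody dose for the CCP units. Even on this reading, dose received is not a baseline modifier.

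**The vaccination sentence naturally applies where the variable varies.** This is fair as a guess at intent. Neither paragraph says so, however, while General principles treats each cohort as its own trial.

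**Stronger inferences that the protocol does not support.** A reader might infer that patients who worsen before the second unit enter the low-dose group as events automatically. Section III-4 requires an overnight stay for progressive COVID-19, with panel adjudication, or death. No section says that admission cancels the second unit, and section VII-1 places it on day 1 or day 2. Dose also varies with unit volume and titre. A reader might also call the absence of timing and serostatus from the list an error. The list is expressly open, so it is not.

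**Conclusion.** The point holds as a fault in a stated analysis. The treatment-by-dose interaction cannot be estimated in either cohort, and the treatment-by-vaccination interaction cannot be estimated in cohort 1. That is two of two planned interactions in cohort 1 and one of two in cohort 2.

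The consequence is limited to subgroup reporting; the primary comparison and its error rate are untouched. The size of any bias in a dose-stratum contrast cannot be derived from the protocol.

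The conclusion assumes that antibody dose means CCP dose, that controls receive no CCP, and that cohort 1 patients meet their eligibility criteria. A few deviations, such as a vaccinated patient randomised into cohort 1 in error, could make a matrix technically full rank but would not give a usable estimate. For cohort 2 it assumes that both vaccinated and unvaccinated patients are enrolled.

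**What to change.** 1. In both Subgroup analyses paragraphs of section X-3, delete the dose subgroup and the treatment-by-dose interaction.
2. Replace them with a dose-response analysis within the CCP arm. Define exposure from the titre and volume of the units first issued for the patient, so that it is fixed before the outcome. Section VIII-1 allocates only the arm; units follow later by ABO compatibility and availability (sections VII-1 and VII-3), so issue is the earliest point at which exposure can be defined. Adjust for baseline factors, report how many CCP patients had no unit issued, and label the analysis non-randomised and exploratory.
3. State that the vaccinal-status subgroup and interaction apply to cohort 2 only.
4. Optionally, add treatment interactions with days from symptom onset and baseline anti-spike serostatus. This is an improvement and not part of the fault.

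The cost is mainly wording. Symptom onset date and baseline serology are already collected. Section VII-4 documents donation number and transfused volume, so capturing issued units for patients never transfused may need one extra data item. Section II-6 accepts several assays on different scales, so titre needs a common scale. The retention samples it already requires, stored partly for comparison between countries, could provide one.

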#### **X-4. Degree of significance**

All tests will be two-sided, with p values of 0.05 or less denoting statistical significance.

#### **X-5. Stopping rules**

- Newly emerging effective treatment for COVID-19 which would substantially change the risk benefit assessment of the investigational approach in this trial compared to alternative options
- Determination of unexpected, significant or unacceptable risk to patients
- Failure to recruit patients at an acceptable rate
- Strong recommendation by the DSMB to the sponsor to stop the trial

#### **X-6. Handling of missing or incoherent**

In the case outcomes would be missing, binary missing outcomes will be treated as treatment failures in interim and primary final analyses, with an imputation by last value carried forward as a sensitivity analysis. For time-to-event outcomes, they will be naturally handled using methods for censored data. No imputation will be used for secondary efficacy and safety outcomes.

#### **X-7. Modifications to the statistical analysis plan**

All modifications to the statistical analysis plan will be discussed between the principal investigator and the methodologist of the trial.

## **XI. DATA HANDLING AND RECORD KEEPING**

### **XI-1. Data collection and entry**

The data is collected on a specific medium in order to differentiate the data used for the study and the source data.

- Data collection

The data is collected in an eCRF. Data collection will be common for all participating countries.

- Computerization of data

For all participating countries, the data is collected via the CleanWEB business application (Telemedicine Technologies, Boulogne Billancourt, France). This solution meets the requirements of the various regulations GCP, ICH, 21 CFR part 11 (FDA) in terms of identification, authentication, traceability, encryption of data flows and data hosting.

### **XI-2. Data transfer**

The data collected in an e-CRF is transmitted in a secure manner (encryption of the data file or encryption of the data flow).

The data to support research results may be shared with the journal / open access for meta-analysis

### **XI-3. Modification, validation and verification of data**

Changes are tracked automatically via an audit trail tracing the identity of the user, logging of the connection, and the nature of the change.

The database lock can only take place after a reconciliation between the monitoring data, the safety data (safety base) and those entered in the CRF (clinical base). This reconciliation allows:

- identify deviations from the protocol;
- identify the patients wrongly included in the regulations;
- measure the CRF completion rate;
- analyse the queries in progress.

Data management is carried out before statistical analysis in a succinct and automatic manner for consistency checks and missing data.

### **XI-4. Record keeping and archiving**

(details in appendix)

## **XII. REGULATORY, ETHICAL CONSIDERATIONS**

### **XII-1. Information and consent of the subject**

The investigator orally informs and gives an information note to each subject, before their inclusion in the trial.

If the subject wishes to participate in the trial, he signs the consent before any intervention or procedure specified in the protocol. The investigator countersigns the consent. The signed and dated declaration of informed consent will remain at the investigator's site and must be safely archived by the investigator so that the forms can be retrieved at any time for monitoring, auditing and inspection

purposes. A copy of the signed and dated information and consent should be provided to the subject prior to participation.

### **XIII. QUALITY ASSURANCE AND QUALITY CONTROL**

A Clinical Research Associate, appointed by the sponsor will ensure the follow-up and the proper conduct of the study, and in particular the review of the written data collected, their documentation, records and reports, in accordance with GCPs as well as the legislative and regulatory provisions in force.

(details in appendix)

### **XIV. PUBLICATION**

The results of the study will be published in general publications.

The authors of the communication or publication will be defined in accordance with the international recommendations: International Committee of Medical Journal Editors "Uniform Requirements for Manuscripts Submitted to Biomedical Journals" Updated October 2007, in the absence of agreement between the investigators.

Appendix Version 2, August 9th 2022

## Authorised medications

The following COVID-19 medications are authorised for use as standard of care in patients enrolled in the study as pre-exposure prophylaxis, post-exposure prophylaxis, as well as early treatment.

### Monoclonal antibodies

- Casirivimab
- Casirivimab/imdevimab (REGN-COV2 or Ronapreve)
- Bamlanivimab
- Bamlanivimab/etesevimab
- Etesevimab
- Imdevimab
- Regdanvimab (Regkirona)
- Sotrovimab (Xevudy)
- Tixagevimab/cilgavimab (Evusheld)

### Antiviral drugs

- Molnupiravir (MK-4482)
- Nirmatrelvir/ritonavir (Paxlovid)
- Remdesivir

These medications must be used according to their approval or according to current treatment guidelines (e.g. for Germany refer to [www.rki.de/covid-19-therapie](http://www.rki.de/covid-19-therapie)).

The study intervention is performed in addition to usual care. If a patient receives both monoclonal antibodies and CCP according to the assignment to the CCP group, the infusion of CCP and monoclonal antibodies may be administered in either order (CCP first or monoclonal antibodies first). However, the infusion of monoclonal antibodies and the transfusion of plasma should not be given simultaneously. To identify and assign acute reactions, a minimum interval of 1 hour must be observed between the end of the administration of one therapy and the start of the next. If an oral antiviral is given in addition to the CCP, the CCP can be transfused any time. Start and end times of administration are documented in the eCRF.

**Centres should ensure that medications used as standard of care are used similarly for patients in both treatment arms. A clinical trial centre's standard of care is determined at the start of the study. Any changes are to be reported to the sponsor.**

Information on standard of care treatment (type of treatment, drug name, start date / end date, dose) will be recorded in the electronic case report form. It will be monitored, and an explanation must be provided in case of deviation from the established standard of care in a clinical trial centre.

## Unauthorised medications

**All other COVID-19 medications are not authorised from the moment of inclusion and up to the study primary endpoint (except if warranted for a reason other than COVID-19).** They may be used once the primary endpoint is reached. There are no unauthorised treatment or medication after achievement of the primary endpoint.

We provide the following list of unauthorised medications as a reference. Unauthorised medications are but not limited to:

- Anti-IL-6R monoclonal antibodies such as tocilizumab
- Baricitinib (JAK 1 and JAK 2 inhibitor)
- Corticosteroids – if given for treatment of COVID-19

